### Study Outcomes and Data Analysis

#### Overview

The primary outcome of the study is a difference in self-reported overall travel-related illness between the intervention and control groups. Secondary outcomes are differences in risk prevention behaviors (Textbox 1) and health risk perceptions (Textbox 2) between the intervention and control groups. The economic cost of travel-related illness symptoms in returning travelers from Bali will also be estimated.

#### Data Analysis: Primary Outcome

Data analysis will be carried out using Epi Info version 7 (Centers for Disease Control and Prevention) and Stata version 12 (StataCorp LP).

The proportion of travelers in the control and intervention groups who self-report illness during their travels, or within two weeks of returning home, will be compared. A univariate analysis will be carried out using Pearson’s chi-square test for comparison of proportions and a *t* test for comparison of mean risk prevention behaviors and knowledge. Logistic regression analyses will be undertaken to estimate the impact of the intervention, while adjusting for other variables such as age, sex, and use of external PTHA, if differences between intervention and control groups are observed at the baseline. Intention-to-treat analysis will be undertaken.

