**Methods:**

Western Australian travelers to Bali will be recruited online before departure and will be randomly allocated to an intervention or control group by computer algorithm. The intervention in this study is a short animated video, with accompanying text, containing PTHA relevant to Bali. An online posttravel survey will be administered to all participants within two weeks of their return from Bali. The primary outcome is the difference in self-reported travel-related illness rates between control and intervention groups. Secondary outcomes include the difference in risk prevention behaviors and health risk knowledge between the control and intervention groups. Further secondary outcomes include whether individuals in the control group who sought external PTHA differ from those who did not with respect to risk prevention behaviors, health risk knowledge, and health risk perception, as well as the rate of self-reported travel-related illness.

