#### Recruitment

Recruitment will take place online, via advertisements promoting the Bali travel survey, strategically located on Facebook and Google pages. The advertisements will run for a 12-month study period to incorporate variation in travel across the year related to seasonal travel or university and school holidays. The advertisements will target people who have searched for Bali flights and/or accommodation online; this information is gathered by Facebook and Google through their single sign-on utility, as well as cookie data to track Internet activity. The main avenue for recruitment is the Internet because a previous study demonstrated that 87% of travelers to Bali make pretravel purchases—flights or accommodation—online [20]. Clicking on the advertisement will take people to a webpage, which briefly describes the study. People interested in enrolling in the study will be asked to enter their departure date, return date, sex, age range, and email address in an online form. This information will allow researchers to determine the age range and sex of those participants who later may be lost to follow-up. Participants will be asked to check a box to indicate that they consent to participate in the study. Travelers can only participate once in the study; multiple enrollments from the same email address will be blocked.

To assist with recruitment, participants will be offered an incentive of entering a lottery to win one AUD $1000 gift voucher or one of 10 AUD $100 gift vouchers. The winning names will be drawn upon study completion. Participants will be informed of the incentive via the online advertisement, consent page, and initial welcome email they receive.

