#### Intervention

All participants will receive an email following enrollment containing a welcome message and a reminder to look for an email within two weeks of their return date. For participants allocated to the intervention group, this email will contain the link to the PTHA intervention.

The intervention in this study is a short, approximately 3-minute, online animated video containing PTHA specific to Bali and Southeast Asia. Topics covered include foodborne illness (eg, Bali belly), mosquito-borne illness (eg, dengue, chikungunya, and Zika), avoiding monkey and canine contact (eg, rabies), and checking measles vaccination status. This video is complemented by PTHA in text below the video and the webpage is optimized for mobile devices. This intervention was developed in consultation with a video producer who has previously created videos for the WA Department of Health. The information in the video and text was developed from a review of the travel-related illness literature, as well as reputable websites such as the Australian government smartraveller.org website [21]. This website was the only PTHA source that showed higher levels of health knowledge among travelers to Bali participating in an airport survey in 2014 [20]. The video producers will provide a *video heat map* that graphs each viewing session (ie, where and when the video was watched, which portions were skipped or watched again, and the percentage of the video that each participant watched). The participant may view the video multiple times, accessing it through the email link. The control group will not receive access to this PTHA video, but they may access PTHA on their own accord.

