#### Posttravel Follow-Up

Within two weeks of the participants’ nominated return dates, they will receive an email containing a link to the posttravel survey, which will be optimized for mobile devices. The control and intervention groups will receive links to surveys that are almost identical, apart from the wording of one question on PTHA. For the intervention group, this question will be phrased to make it clear they are being asked about PTHA received external to this study (ie, PTHA from their general practitioner or from their own Internet search). If the participant does not complete the survey within a week, a second email will be sent to the participant.

The survey will contain questions in six general themes: (1) information about their trip to Bali, (2) PTHA behaviors, (3) risk prevention behaviors (sample question presented in Textbox 1), (4) knowledge about disease risk (sample question presented in Textbox 2), (5) illness and symptoms during and/or posttravel, and (6) basic demographic information. The survey was adapted from a 2014 WA traveler survey [20] and will take participants, on average, between 5 and 10 minutes to complete, depending on whether or not illness is reported. The final survey and intervention were developed in consultation with WA Department of Health staff and pilot-tested, with the intervention, by a focus group in late 2015.

Posttravel survey sample questions. Participants will be asked to report the health risk-prevention behaviors they engaged in during travel. Participants may choose from the following responses: Daily, Every 2-3 days, Once a week, and Never.Please answer the following questions about your behavior during your recent trip to Bali.How often did you use insect repellent on this trip?How often did you use alcohol-based hand sanitizer on this trip?How often did you use a mosquito net on this trip?How often did you use mosquito protective clothing on this trip? (eg, long sleeves)How often did you eat eggs with a runny yolk on this trip? (eg, fried egg on top of fried rice)How often did you eat fresh fruit you did not peel yourself on this trip?

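### The primary outcome runs to two weeks after return, but the only survey is sent within those two weeks, so anyone who answers before day 14 is incompletely observed.

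*Protocol article*

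**What the plan says.** Under Data Analysis: Primary Outcome, the protocol article compares the proportions of travelers in each arm "who self-report illness during their travels, or within two weeks of returning home, will be compared". The outcome therefore covers the trip plus 14 days.

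The timing of the survey is given three times, each time as an upper limit:

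- Posttravel Follow-Up: "Within two weeks of the participants’ nominated return dates, they will receive an email containing a link to the posttravel survey".
- Abstract, Methods: "An online posttravel survey will be administered to all participants within two weeks of their return from Bali".
- Intervention: the welcome email carries "a reminder to look for an email within two weeks of their return date".

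The only further contact about the survey goes to people who have not finished it: "If the participant does not complete the survey within a week, a second email will be sent to the participant". The survey theme on illness is listed as "5) illness and symptoms during and/or posttravel", with no number of days. The return date that drives the email is collected at enrollment, before travel, where people are "asked to enter their departure date, return date, sex, age range, and email address in an online form".

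**The concern.** A single survey cannot observe a period that has not yet elapsed. If the link goes out on, say, day 5 and is answered at once, illness starting on days 6 to 14 belongs to the primary outcome but cannot be reported. The planned analysis is a comparison of proportions, so that participant counts as a non-case. The length of window actually observed then varies with the send day and with how quickly each person answers.

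Three results are at stake. The cumulative incidence of illness and the cost-of-illness estimate, both taken from all participants, would be too low. The absolute difference between arms, on which the sample size rests, could shrink. If one arm tended to answer sooner than the other, the two arms would also be observed for different lengths of time.

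**Working it through.** **1. Does anything in the article close the gap?** The reminder reaches only non-completers, so an early completer is not asked again. The health care provider interviews (Posttravel Follow-Up) concern participants who have already reported seeking medical attention, so they do not pick up illness that starts after the survey. The adjustment variables named for the logistic regression (age, sex, use of external advice) are examples, and days observed is not among them. No minimum interval before sending is stated. A return date that changes after enrollment adds further variation.

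**2. Share of the 14-day post-return window observed**, by completion day d, is min(d, 14)/14:

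| Completion day | Share observed |
|---|---|
| 1 | 7% |
| 3 | 21% |
| 7 | 50% |
| 10 | 71% |
| 14 or later | 100% |

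**3. The plan's own sample size** (Sample Size Calculation: 40% v 30%, 80% power, 0.05, taken as two-sided):

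n per arm = [1.96 × √(2 × 0.35 × 0.65) + 0.8416 × √(0.40 × 0.60 + 0.30 × 0.70)]² / 0.10² = (1.3221 + 0.5646)² / 0.01 = 356.

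This matches the stated 356 per arm and 712 completers. Dividing by 0.5 for loss to follow-up gives 1424. These figures are correct and do not depend on this point.

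**4. Illustrative effect on power.** The article gives neither the share of first illnesses that start after return (s) nor the send days. Assumptions:

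- The 40% includes post-return illness.
- s is 10% to 30%, with onset spread evenly over the 14 days.
- Everyone completes on day d.
- The loss and the relative effect are the same in both arms.

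The fraction of cases lost is s × (14 − d)/14, and both planned rates are multiplied by one minus that fraction. For d = 7 and s = 30%, the loss is 0.30 × 7/14 = 0.15, and the rates become 0.40 × 0.85 = 34.0% and 0.30 × 0.85 = 25.5%. Power at 356 per arm, by the same formula:

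| Completion day | s | Rates | Power |
|---|---|---|---|
| 7 | 10% | 38.0% v 28.5% | 76.9% |
| 7 | 30% | 34.0% v 25.5% | 69.9% |
| 10 | 10% | 38.9% v 29.1% | 78.2% |
| 10 | 30% | 36.6% v 27.4% | 74.5% |
| 14 or later | any | 40% v 30% | 80.0% |

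**5. Differential timing, if it occurred.** With no true effect, a 40% rate, and mean completion days that differ by Δ (both before day 14), the spurious difference is 0.40 × s × Δ/14. With s = 10% and Δ = 1 this is 0.3 percentage points. With s = 30% and Δ = 3 it is 2.6 points. The planned difference is 10 points.

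**The case against.** The best counter-argument concerns the base for the power figures. The 40% is attributed to a source that the Introduction describes as giving rates of health impairment among people while traveling. On that description, 40% is an in-travel rate. Everyone who answers after returning has completed that period, and partly observed post-return illness would add to 40% instead of being taken from it. The power loss in step 4 would then not arise. This stands, and it is why those figures are illustrations only.

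Second, the send day is not stated. A link sent on exactly day 14 satisfies the text and truncates nobody, and a condensed article may leave the operational day to the full protocol. That is fair as to the size of the problem. It does not make the wording right: the article states both the outcome window and the survey timing, and as written the timing permits what the window rules out. No analysis plan can recover illness that starts after the only survey.

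Third, a reader might infer that every participant's window is cut short, or that the comparison between arms is biased. The document supports neither. Respondents on or after day 14 are fully observed. Both arms are randomized and share one survey and reminder schedule, so equal truncation leaves the test valid under the null and, under the proportional model above, leaves the relative effect unchanged. Only the intervention arm receives a health video, so a difference in response speed is conceivable, but nothing in the article shows one.

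**Conclusion.** The point holds: the survey timing as written does not fit the primary outcome. The outcome is incompletely observed for anyone who completes the survey before day 14, and post-return illness is under-counted to an extent that depends on send day and response day. Incidence and cost of illness are understated to that extent. The absolute treatment difference may be diluted, and bias between arms is conditional on a difference in response timing.

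The mismatch itself rests on the article's text alone. Its size rests on assumptions the article cannot confirm: the share and spread of post-return onsets, the completion day, and whether 40% includes post-return illness. Subject to these, power would be about 77-70% at day 7 and unchanged at day 14 or later. The figures do not show that the trial is underpowered, and the planned sample size needs no change once the window is fully observed.

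**What to change.** Send the survey link no earlier than day 14 after the return date, with the reminder a week later (day 21 if the link goes on day 14). Word the illness questions to cover the trip and the period up to day 14 only, so that late responders do not get a longer window. Make sure the completion date and the illness onset date are recorded; the full questionnaire is not shown, so these items may already exist. Correct the three statements of survey timing to match.

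For participants already surveyed before day 14, compare the arms over a window that all respondents had completed, as the primary comparison or as a sensitivity analysis. With no minimum send interval, that window may have to be illness during travel only.

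The cost is a changed send date for the email and possibly one or two survey items. Recall of trip behaviors and early symptoms becomes slightly longer, and response may fall a little, in a trial that already allows for 50% loss.

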#### Randomization

Randomization will be performed using a custom-built computer algorithm. Participants will be randomly allocated into control or intervention groups after completion of the online enrollment form, and the allocation will be sent to the email management program (MailChimp) used in the study. A block randomization (block size=4) with a uniform 1:1 allocation will be used.

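### Use of external PTHA is named as a covariate for the randomised comparison under a baseline condition, but the article describes it as measured only after travel; adjusting for it can bias the intervention effect

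*Protocol article*

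**What the plan says.** All references are to the Protocol article.

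- **Data Analysis: Primary Outcome.** Illness proportions are compared by Pearson's chi-square test. Logistic regression is then to estimate the impact of the intervention "while adjusting for other variables such as age, sex, and use of external PTHA", with the condition "if differences between intervention and control groups are observed at the baseline". The same paragraph commits to intention to treat.
- **Recruitment.** Interested people are "asked to enter their departure date, return date, sex, age range, and email address in an online form". None of these items concerns PTHA.
- **Randomization.** "Participants will be randomly allocated into control or intervention groups after completion of the online enrollment form".
- **Intervention.** The welcome email carries the video link for the intervention arm. The video's topics include "checking measles vaccination status". Controls do not get the video but are free to find advice themselves.
- **Posttravel Follow-Up.** PTHA behaviours are one of six themes in a survey sent after return; illness is another. The two arms' surveys differ in a single item, which concerns advice obtained before travel. The article explains the difference as follows: "For the intervention group, this question will be phrased to make it clear they are being asked about PTHA received external to this study".

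**The concern.** A covariate that balances a randomised comparison should be fixed before allocation, or be something the intervention cannot change. As described, external PTHA is neither. It is recorded after allocation, after the video link and after the trip, in the same questionnaire as the illness outcome. Nothing described separates advice sought before enrolment from advice sought afterwards.

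Age range and sex can differ between randomised arms only by chance. External PTHA can also differ because the video sent someone to a doctor to check vaccination status, because it replaced their own search, or because the question is put differently to the two arms. Conditioning on it can remove the part of the video's effect that runs through advice-seeking. It can also make the arms unlike each other, within levels of external PTHA, on whatever drives people to seek advice. The adjusted estimate would then no longer be the intention-to-treat effect that the plan promises.

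**Working it through.** **1. The plan's own figure.** Sample Size Calculation: 40% versus 30%, 80% power, P = .05 (two-sided reproduces the figure), 1:1.

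n per arm = [1.960·√(2·0.35·0.65) + 0.8416·√(0.40·0.60 + 0.30·0.70)]² / 0.10² = 355.9, so 356. Then 2 × 356 = 712 completers, and 712 / 0.5 = 1424 enrolled. All three match the article. They rest on an unadjusted comparison of two proportions, so the covariate question does not touch them.

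**2. Order of events.** Enrolment form (dates, sex, age range, email) → allocation → email, with the video link in one arm → trip → survey containing both external PTHA and illness. The baseline condition can be checked for sex, age range and planned dates. It cannot be checked for external PTHA, because no baseline value is described. Either the condition is never met for that variable, and naming it is an error, or the posttravel answer is treated as if it were baseline.

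**3. What the second reading can do: illustration with assumed inputs.** Let A be arm, E external PTHA, and U unmeasured health awareness (0 or 1, half each):

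- P(E=1) = 0.40 + 0.15A + 0.30(U − 0.5)
- P(ill) = 0.40 − 0.05A − 0.10(E − 0.40) − 0.10(U − 0.5)

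Intention-to-treat difference = −0.05 − 0.10 × 0.15 = −0.065.

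Within levels of E, the mean of U differs by arm:

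| Stratum | Mean U, control | Mean U, intervention | Risk difference |
|---|---|---|---|
| E = 1 | 0.5·0.55/0.40 = 0.6875 | 0.5·0.70/0.55 = 0.6364 | −0.05 − 0.10(0.6364 − 0.6875) = −0.0449 |
| E = 0 | 0.5·0.45/0.60 = 0.3750 | 0.5·0.30/0.45 = 0.3333 | −0.05 − 0.10(0.3333 − 0.3750) = −0.0458 |

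Averaged over the pooled E (0.475): 0.475(−0.0449) + 0.525(−0.0458) = −0.0454. With U uniform on 0 to 1 instead, the result is −0.0485. Between 25% and 30% of the effect is lost.

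Same model, other inputs:

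| Assumption | ITT | Adjusted, binary U | Adjusted, uniform U |
|---|---|---|---|
| No direct effect, PTHA effect −20 points | −3.0 | +0.5 | +0.15 |
| No effect of video or PTHA on illness | 0 | +0.5 | +0.15 |

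**4. Second illustration.** Large-sample logistic fits. Control uptake is assumed at 48%, the article's global average for professional PTHA (it says Australians fall below this). External PTHA is assumed to lower illness risk by 10 or 20 points; the article cites a reduction of about 20% for a travel doctor visit without saying whether it is absolute.

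- *Mediation, direct effect −5 points.* Intervention-arm uptake of 38%, 58% or 68% gives ITT differences of −3 to −4, −6 to −7, or −7 to −9 points. The adjusted difference is −5 in every case. At 68% and 20 points, the odds ratio is 0.67 unadjusted and 0.79 adjusted.
- *Wording only, no video effect, equal true uptake, 20-point PTHA effect.* If 10%, 20% or 30% of intervention-arm non-users are recorded as users, a true odds ratio of 1.00 becomes 1.04, 1.09 or 1.13.
- *Equal uptake and equally accurate reporting.* The risk difference is −5 points with or without adjustment.

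**The case against.** Several points weigh against making this larger than it is.

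- The covariates are given as examples and the adjustment is conditional. A reader might infer that the primary analysis as a whole is biased. The text does not support that: the chi-square comparison, on which the sample size rests, uses no covariates and is untouched.
- Read literally, the baseline condition would keep external PTHA out altogether. That is fair, and it is why the firm criticism is internal inconsistency. Bias follows only if the survey answer is treated as baseline, but naming the variable invites that.
- A reader might infer that the different wording does misclassify one arm. The article gives its purpose: to stop intervention participants counting the study video. Controls receive no study advice, so all of theirs is external, and the wording may bring the two arms' answers closer in meaning. The question texts are not shown, so it may add differential error; it cannot be said that it does.
- Nothing in the article shows that a video of about 3 minutes shifts external advice-seeking, and some of that advice may precede enrolment.
- The change of sign in the illustration should not be read as a finding. The adjusted values of +0.15 to +0.5 points are practically zero against a standard error of √(0.40·0.60/356 + 0.30·0.70/356) = 3.6 points.

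These points limit the size and certainty of the concern. None gives external PTHA a baseline value or makes it a sound covariate for the randomised contrast.

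**Conclusion.** The point holds in a limited form. The rule in Data Analysis: Primary Outcome names a variable with no described baseline value under a baseline condition. If the posttravel answer is used, the regression meant to estimate the intervention's impact can depart from the intention-to-treat effect, and the variable would enter just when the arms differ on it. Size and direction are unknown. The shifts shown above rest on assumed uptake, PTHA effect and awareness, and the bias in the risk difference vanishes if uptake and reporting are equal by arm.

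**What to change.** Delete use of external PTHA from the adjustment set for the randomised comparison. Restrict that set to variables known before randomisation (age range, sex, planned dates) or fixed characteristics that the video cannot change, even if recorded later. Report external PTHA by arm descriptively, with a note that the question is worded differently in the two arms. The control-group comparisons of those who did and did not seek advice, under Data Analysis: Secondary Outcomes, stay as planned.

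The cost is one line in the analysis text. No new data are needed, and the 356 per arm and 1424 enrolled do not change.

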### Rates of Travel-Related Disease in Returning Travelers

Reported rates of travel-related illness vary, with studies estimating that 22-64% of travelers experience some form of health impairment while traveling, depending on the destination and season of travel [3]. In Western Australia, almost 8% of communicable disease notifications are for illnesses acquired overseas. From 2006 to 2015, the proportion of overseas-acquired infections in Western Australia attributed to travel to Indonesia rose from 10% to 42% (personal communication from [name], Data Custodian for the Western Australian Notifiable Infectious Diseases Database at the Western Australian Department of Health, April 7, 2016) [4]. The most common notifiable diseases acquired in Indonesia are dengue fever and gastroenteritis caused by *Campylobacter* and *Salmonella* species [4].

Establishing an accurate picture of travel-related infections is difficult due to underdiagnosis and under-reporting, the highly transient nature of international travel, and the emergence of new disease risks in travel destinations. In particular, while notifiable disease data are available, there are no comparable data available for non-notifiable illnesses, such as traveler’s diarrhea, among residents returning to Western Australia.

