#### Sample Size Calculation

The sample size calculation was based upon the online PTHA intervention lowering the rate of self-reported illness in Western Australians returning from Bali by 10%. Existing literature suggests that reduction in illness as a result of visiting a travel doctor before departure is approximately 20% [13,14]. The sample size calculation assumed an illness rate of 40% in the control group [3], with a reduction of 10% in the intervention group, detected at 80% power with a *P* value of .05. A sample size of 712 participants completing the study—356 control and 356 intervention participants—was determined using PS: Power and Sample Size Calculation statistical software [25]. Assuming approximately 50% of participants are lost at follow-up, which is the average for Internet-based trials [26], and although we expect less loss because of the incentive, at least 1424 participants—712 exposed and 712 unexposed participants—would need to be enrolled in the study.

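### Adjustment of the primary comparison depends on an undefined baseline imbalance, and the plan does not say whether the unadjusted or the adjusted result leads

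*Protocol article*

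**What the plan says.** In the Protocol article, the section Data Analysis: Primary Outcome sets out two analyses of self-reported illness. Pearson's chi-square test on the two proportions is planned without condition. Logistic regression is planned to estimate the intervention effect with adjustment, "if differences between intervention and control groups are observed at the baseline". Age, sex and use of external pretravel health advice are given as examples of covariates, so the list is open. The section does not define a baseline difference and does not rank the two results.

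Other sections bear on this:
- Recruitment: before allocation, participants "will be asked to enter their departure date, return date, sex, age range, and email address in an online form".
- Randomization: allocation follows completion of that form. "A block randomization (block size=4) with a uniform 1:1 allocation will be used".
- Posttravel Follow-Up: external advice is asked about in the survey after return, and that question is worded differently in the two arms.
- Rates of Travel-Related Disease in Returning Travelers: illness rates across studies vary "depending on the destination and season of travel".
- Sample Size Calculation: the plan "assumed an illness rate of 40% in the control group", "with a reduction of 10% in the intervention group".

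**The concern.** Among all randomised participants, baseline differences between the arms arise by chance. Their presence says nothing about whether a covariate affects illness, and adjustment helps only for covariates that do. A strong predictor that happens to be balanced would be left out, while a covariate unrelated to illness could be brought in because it happened to differ.

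With no threshold, no closed list and no ranking, someone who has seen both results could decide which one to present as the main finding. That is the main exposure, and it does not depend on any assumed covariate strength.

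The choice of covariates adds two problems. Planned trip length and season of travel can be derived from the form completed before allocation, yet neither is named. External advice is named in a sentence about baseline differences, but it is not on the enrolment form and is measured only after travel. Seeing the video could change whether a participant seeks other advice. Adjusting for it could therefore remove part of the intervention effect or bias the comparison.

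**Working it through.** **1. The plan's own figure.** Inputs from Sample Size Calculation are 40% v 30%, a significance level of 0.05 (taken as two-sided, which is not stated) and 80% power.

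n per arm = [z(0.975)·√(2·p̄·q̄) + z(0.80)·√(p1q1 + p2q2)]² / (p1 − p2)², with p̄ = 0.35

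= [1.960·√0.455 + 0.842·√0.450]² / 0.10² ≈ 356

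This matches the stated 356 per arm and 712 completers. With 50% loss, 712/0.5 = 1424, also as stated. The calculation is for an unadjusted comparison, and a change to the adjustment rule leaves it as it is.

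**2. How often chance alone would trigger adjustment.** The article gives no threshold. If a difference meant p < 0.05 on any of k independent covariates, the probability is 1 − 0.95^k:
- k = 2: 9.8%
- k = 3: 14.3%
- k = 4: 18.5%
- k = 5: 22.6%

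**3. Error rate and power by simulation.** There were 6000 trials per scenario with 356 per arm and complete follow-up, at marginal rates of 40% v 40% (null) and 40% v 30% (alternative). These values are assumptions and are not in the article: age odds ratio 0.8 per SD, sex odds ratio 1.2, one trip-date covariate with odds ratio 1.0 to 2.0 per SD, and a trigger of p < 0.05 on age or sex. Monte Carlo standard error is √(0.8·0.2/6000) ≈ 0.5 point for power and √(0.05·0.95/6000) ≈ 0.003 for type I error.

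Type I error:

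| Trip-date OR per SD | Chi-square | Imbalance rule | Better of chi-square and age/sex model | Best of three, adding the trip-date model |
|---|---|---|---|---|
| 1.0 | 0.0520 | 0.0520 | 0.0575 | 0.0583 |
| 1.2 | 0.0482 | 0.0483 | 0.0537 | 0.0570 |
| 1.5 | 0.0497 | 0.0500 | 0.0538 | 0.0612 |
| 2.0 | 0.0517 | 0.0513 | 0.0555 | 0.0672 |

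Power:

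| Trip-date OR per SD | Chi-square | Imbalance rule | Always adjust (age, sex, trip-date) | Gain over chi-square, points |
|---|---|---|---|---|
| 1.0 | 80.3% | 80.4% | 80.6% | 0.3 |
| 1.2 | 80.2% | 80.3% | 80.9% | 0.7 |
| 1.5 | 79.4% | 79.5% | 81.4% | 2.0 |
| 2.0 | 80.1% | 80.0% | 83.9% | 3.7 |

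The imbalance rule behaves almost exactly like the plain chi-square: nominal error and no useful gain in power. The last two columns of the first table show what free choice among results could do.

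**4. Why the trip dates are candidates.** The outcome covers the trip and the two weeks after return, so a stay of L nights gives a window of about L + 14 days. Eligibility starts at one night and no upper limit is stated, so planned length varies and time at risk varies with it.

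**5. Scale.** At the planning rates the risk difference is 10 points, the risk ratio is 0.30/0.40 = 0.75, and the odds ratio is (0.3/0.7)/(0.4/0.6) = 0.64. The sample size is set in proportions, while the logistic model reports the last of these.

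**The case against.** Several stronger readings are tempting, and the article does not support them.

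- *The adjusted model replaces the chi-square.* The chi-square is planned unconditionally and only the adjustment is conditional. The gap is that neither result is named as leading.
- *The rule inflates type I error.* Applied mechanically it does not (0.048 to 0.052). The figures of 0.054 to 0.067 require an analyst to pick the most favourable model, which the article does not propose. They show what the wording leaves open.
- *Trip dates are ignored.* The covariates are given as examples, so trip length and season are unnamed but not excluded. A closed list could sit in a fuller document. The imbalance condition, however, is stated here and is a poor rule as written.
- *The article shows that season drives illness in Bali.* Its 22-64% range is attributed jointly to destination and season. It isolates no season effect for Bali and gives no relation between trip length and illness. The size of any gain is therefore assumed.
- *An odds ratio contradicts the planned outcome.* It does not. Proportions are compared directly by the chi-square, and an adjusted odds ratio beside them is conventional.

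Two further objections have some force. Blocks of four over a 12-month recruitment keep the arms close in enrolment time, which limits seasonal imbalance as far as travel follows enrolment. But a balanced predictor is exactly what an imbalance trigger would pass over. Also, outcomes exist only for survey responders. With about 50% loss allowed for, differences among responders may reflect attrition as well as chance. That is a further reason to fix the adjustment set from enrolment variables, which are known for everyone randomised.

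**Conclusion.** The point holds, at modest size. The article ties adjustment to an undefined imbalance, does not say which result leads, and names a post-travel variable as if it were baseline. These are faults in the stated rule and rest on no assumed figure.

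The numerical consequences are small. Error is near nominal if the rule is followed mechanically. The power forgone is about 0 to 4 points for assumed trip-date odds ratios of 1.0 to 2.0 per SD, and essentially none if trip dates do not predict illness. The simulations assume 356 responders per arm and model no differential loss. The sample size reproduces exactly and does not need to change. The change is worth making because it closes off a choice after seeing the data and costs almost nothing, not because the planned analysis would be invalid.

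**What to change.** Delete the conditional clause and name one primary analysis: a logistic model with arm, age range, sex, planned trip length and season of planned travel, all taken from the enrolment form and fitted whatever the observed balance. Define trip length as planned return date minus planned departure date, and fix the season categories in advance. Leave external pretravel advice out of this model and say why: it is measured after allocation and could be affected by it. Keep the unadjusted chi-square as a supportive analysis.

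Preferably report a standardised risk difference with a 95% confidence interval from the same model beside the odds ratio, so that the result can be read on the 40% v 30% planning scale. This is a reporting preference and corrects no error.

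The cost is a change of wording, dated before outcomes are compared by arm. Every variable in the model is already collected, and neither enrolment nor the survey changes.
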